**3.7.1.4 Sample size**

Sample size was estimated based on a previous study showing that the complete healing rate of LDA-induced mucosal breaks was 58% in patients who took misoprostol, a PGE1 analog, for 8 weeks. The following assumptions were made for sample size calculation: (1) the wound-healing effect of a triple dose of rebamipide was equal to that of misoprostol; (2) the complete healing rates in the placebo and rebamipide groups were 20% and 58%, respectively; (3) 10% of patients in each group will either drop out or have unsatisfactory follow-up VCE images. We calculated that at least 30 patients were needed in the rebamipide group to give the study 90% power at a 5% significance level by a test of proportions.

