**3.3.5 Method and Period of Administration**

1) Patients with small intestinal damage among those taking Bayaspirin will be randomized into two groups (groups A and B). Capsule endoscopy will be used in the diagnosis of the small intestine. A separately specified controller will perform the allocation.

2) Randomization

Subjects will take the randomly assigned test drug during the study.

Dynamic allocation by using the minimization method will be applied in randomization, and subjects will be allocated to each of the two groups in the study. Drug numbers and information on the allocated groups will be managed by the allocation controller, and will be disclosed when the data are fixed after the completion of the study.

3) Allocated groups and drug administration method:

Group A: Three tablets per dose of control (placebo) tablet (100 mg lactose) will be taken three times daily after every meal.

Group B: Three tablets per dose of rebamipide tablet (100 mg rebamipide) will be taken three times daily after every meal.

4) Administration period: 8 weeks

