**3.7.1.2 Method of analysis of the primary and secondary endpoints**

The Wilcoxon signed-rank test (for continuous data) or McNemar test (for ordinal data) was used for comparisons of data between baseline and 8 weeks. Differences with P-values <0.05 were considered significant.

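### The stated 90% power is not delivered: with the planned 30 rebamipide and 15 placebo patients, two-sided power for 58% v 20% is about 60–70%

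*Protocol*

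**What the plan says.** Section 3.7.1.4 bases the size of the trial on complete healing of mucosal breaks. It assumes that "the complete healing rates in the placebo and rebamipide groups were 20% and 58%, respectively", and that "10% of patients in each group will either drop out or have unsatisfactory follow-up VCE images". From this it concludes that "at least 30 patients were needed in the rebamipide group to give the study 90% power at a 5% significance level". The method named is only a test of proportions. The section gives no placebo size, allocation ratio or sidedness.

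The placebo size appears only in the design diagram of section 3.3.6 (Contents and Schedule of Examination), which labels Group A with 15 patients and Group B with 30. Section 3.3.5 identifies the arms: "Group A: Three tablets per dose of control (placebo) tablet (100 mg lactose) will be taken three times daily after every meal". Group B is rebamipide. The planned allocation is therefore 2:1 in favour of rebamipide, 45 patients in all.

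**The concern.** The power of a two-group comparison depends on both arms, and the smaller arm limits it. Thirty patients on one side of a 58% v 20% comparison looks like the result for equal arms, yet the diagram has half as many controls. If so, the 90% belongs to a design that is not the one planned.

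Ethics committees and readers rely on the stated power. If the trial found no difference, a reader who trusted 90% would take this as fairly strong evidence that rebamipide does not heal at the assumed rate. The planned design cannot support that reading.

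**Working it through.** **Inputs.** Healing 0.20 (placebo) and 0.58 (rebamipide), so d = 0.38; 5% level; 10% loss per group (all from 3.7.1.4). Arms of 15 and 30 (3.3.6, with 3.3.5 for which is which). After loss, 30 × 0.9 = 27 and 15 × 0.9 = 13.5, so 13 or 14. Sidedness is not stated. I take two-sided as the ordinary reading of a 5% level and of "Differences with P-values <0.05 were considered significant" in 3.7.1.2, and show one-sided as well.

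**Can the stated 30 be reproduced?** The pooled normal formula for the placebo arm, with r rebamipide patients per placebo patient and p̄ = (0.20 + 0.58r)/(1 + r), is

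n = [z_α √(p̄(1−p̄)(1+1/r)) + z_β √(0.20×0.80 + 0.58×0.42/r)]² / d²

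- Equal arms, one-sided: p̄ = 0.39; n = [1.645 × 0.690 + 1.282 × 0.635]² / 0.1444 = 26.3, so 27 per arm. Then 27/0.9 = 30 per arm, which matches the stated figure.
- Equal arms, two-sided: 32.5, so 33 per arm, or 37 after loss. The unpooled formula gives 29.4, about 30 per arm, but before any loss.
- 2:1, two-sided: p̄ = 0.4533; n = [1.960 × 0.610 + 1.282 × 0.531]² / 0.1444 = 24.4, so 25 placebo and 50 rebamipide evaluable, or 28 and 56 enrolled.
- 2:1, one-sided: 20 placebo and 40 rebamipide evaluable, or 23 and 45 enrolled.

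The figure of 30 appears only with equal arms. At 2:1 the most lenient variant (one-sided, unpooled) still needs about 34 rebamipide and 17 placebo patients before loss.

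**Power of the planned design.** Power = Φ[(d − z_α·SE₀)/SE₁], where SE₀ is the pooled and SE₁ the unpooled standard error.

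- 30:15, two-sided: SE₀ = 0.1574, SE₁ = 0.1371; (0.38 − 1.960 × 0.1574)/0.1371 = 0.521; Φ = 69.9%.
- 27:14, two-sided: SE₀ = 0.1639, SE₁ = 0.1430; (0.38 − 1.960 × 0.1639)/0.1430 = 0.412; Φ = 66.0%.

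Other tests, with the chi-square, Fisher and Yates rows computed by exact binomial enumeration:

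| Test at 5% | 30:15 | 27:14 | 27:13 |
|---|---|---|---|
| Two-sided, pooled normal | 69.9% | 66.0% | 63.5% |
| Two-sided, chi-square (exact) | 69.7% | 66.7% | 64.0% |
| Two-sided, Fisher | 61.9% | 60.3% | 61.0% |
| Two-sided, Yates | 60.1% | 56.9% | 52.0% |
| Two-sided, arcsine | 72.0% | 68.5% | 66.4% |
| Two-sided, unpooled Wald | 79.2% | 75.7% | 74.0% |
| One-sided, pooled normal | 81.1% | 78.0% | 76.1% |
| One-sided, chi-square (exact) | 82.9% | 79.3% | 78.3% |
| One-sided, Fisher | 69.7% | 66.6% | 63.9% |
| One-sided, unpooled Wald | 87.0% | 84.4% | 83.1% |

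No cell reaches 90%.

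**How far off is it?** With 27:14 and the two-sided pooled test, 90% power needs a rebamipide healing rate of about 70%; with Fisher's test, about 73%. With 30 rebamipide patients and 58% healing, 90% two-sided needs about 36 evaluable placebo patients.

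**The case against.** Five points can be made on the other side.

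- **Sidedness and test are not stated.** The 60–70% applies to the two-sided chi-square and Fisher tests. One-sided, the pooled formula gives 81% before loss and 76–78% after, so a miss rate of 19–24%. Other two-sided approximations give up to 79%. This stands as a reason to label the range. It does not rescue 90%, since the most favourable variant, before loss, gives 87%.
- **The equal-arm origin of the 30 is inferred.** It is. The protocol does not show its calculation, and two equal-arm routes come out near 30. The error does not depend on which was used.
- **The placebo size rests on one diagram label.** True. But the label is clear, the arm is identified in 3.3.5, and nothing else in the protocol gives another number.
- **The study is an exploratory pilot (section 2).** A pilot need not have 90% power. This one claims it, and a wrong figure misleads more than none.
- **Complete healing is a secondary endpoint (3.4.2).** So the figures here are not the power for the primary endpoint, the number of mucosal breaks. That mismatch is a separate point. Complete healing is still the only endpoint on which the size is justified, so the claim should be true there.

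**Conclusion.** The concern holds. On the protocol's own healing rates, loss and arm sizes, 90% power is not reached by any of the tests tried, one- or two-sided, even before loss. For a two-sided 5% chi-square or Fisher test the power is 62–70% as enrolled and 60–67% after 10% loss, so the chance of missing the assumed effect is roughly 30–40% rather than 10%. One-sided, by the pooled formula, that chance is 19% before loss and 22–24% after.

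This rests on reading the diagram in 3.3.6 as the planned enrolment, and on two-sided testing for the headline range. Sections 3.3.6 and 3.7.1.4 contradict each other as written and must be reconciled.

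**What to change.** Rewrite section 3.7.1.4 for the design planned. Give both arm sizes (30 and 15, about 27 and 14 evaluable), the 2:1 ratio, the test and its sidedness, and the power that follows. Delete the 90% claim. If the test is two-sided, suitable wording would be: *With 30 rebamipide and 15 placebo patients, of whom about 27 and 14 are expected to be evaluable after 10% loss, the study has about 66% power (chi-square test, two-sided 5%; 60% by Fisher's exact test) to detect complete healing of 58% v 20%.* If a one-sided test is meant, say so and give about 78% (pooled normal formula). Either way, state that the figure concerns complete healing.

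If the diagram is wrong and equal arms of 30 were intended, correct the diagram instead. Power with 27 evaluable per arm would then be 84% two-sided or 91% one-sided by the pooled formula, and the sidedness would still have to be stated.

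The main change costs one paragraph and needs no extra patients, no new endpoint and no change of analysis. The only drawback is a less favourable stated power.

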**4. Ethics**

This study will be conducted in accordance with the Declaration of Helsinki, an ethical guideline for clinical studies.

**4.1 Consent of Subjects**

Before the study, the investigator, etc., will provide an adequate explanation on the contents of the study to the subject, on the basis of the informed consent form approved by the institutional review board of the study institution, and will obtain the signed written consent form from the subjects. The informed consent form will contain the contents specified in the standards stipulated in Article 14, Paragraph 3, and Article 80-2 of the Pharmaceutical Affairs Law (“Standards for the Implementation of Clinical Trials of Pharmaceutical Products” [GCP] [Ordinance No. 28 of the Ministry of Health and Welfare]).

**4.2 Institutional Review Board of the Study Institution**

Members of the institutional review board established by the head of the study institution will review the submitted protocol, informed consent form, etc. from the ethical, scientific, and medical standpoints; express their opinions in writing; and forward their report to the head of the study institution. The document containing their opinions will clearly specify the reviewed study, reviewed materials, date of review, and approval of the study. Deviations from the protocol or partial amendments to the protocol because of medically unavoidable reasons (e.g., to avoid risks to subjects) will be reported to and approved by the institutional review board.

**5. Monetary Payment and Medical Security**

In this clinical study, a partial self-pay burden will be applied for consultation and examinations, as in routine clinical practice; however, expenses for drugs used in the clinical study will not be borne by patients. In addition, there will be no special increase in expenses due to participation in the study.

If health hazards such as adverse reactions occur in patients during the clinical study, the physicians will perform appropriate consultation and treatment. Health insurance will be used. However, if health hazards occur in patients due to participation in the study, the treatment expenses will be paid by the hospital, and thus there will be no financial burden to the patients.

In conducting this clinical study, we have taken out the liability insurance offered by Tokyo Marine & Nichido Fire Insurance Co., Ltd. for clinical studies. If unpredictable serious health hazards occur and a causal relation to the study is revealed, compensation payment will be made depending on the degree of damage. The specific contents of compensation are shown in the Appendix.

**6. Changes in the Contents of the Protocol**

If changes to the protocol become inevitable after the initiation of the study, the study implementation manager will collaborate with the principal investigator and determine the contents to be changed. Changes can be made to an extent that is not deviating from the objective of the study.

**7. Study Period**

Case accumulation period: After approval to August 31, 2014

